## Abstract

**Background:**

Mild cognitive impairment (MCI) and Alzheimer’s disease (AD) might be more frequent in patients with inflammatory bowel disease (IBD), but the relationship between these 2 entities is yet to be entirely established. Certain blood biomarkers (eg, serum amyloid A [SAA] and serum homocysteine [Hcy], which increase in IBD and MCI; brain-derived neurotrophic factor [BDNF], which decreases in MCI and AD but is not clearly modified in IBD; and S100 calcium-binding protein B [S100B], which increases in the blood-brain barrier and neuronal lesions) might predict the stage of MCI or dementia or progression to a further state. The gut–brain axis (GBA) might be the key to the development of MCI in patients with IBD, along with systemic inflammation and the possible and unknown adverse effects of disease-modifying medication.

**Objective:**

The aim of this study is to investigate whether GBA interactions play a role in MCI development in patients with IBD.

**Methods:**

A case-control study will be conducted on at least 100 patients diagnosed with IBD, matched with 100 healthy individual controls. The matching will include sex, age, and education. Patients will be fully examined, and a full interview and a neurological and cognitive examination will be performed. The primary clinical outcomes will be cognitive test scores (Montreal Cognitive Assessment, Trail Making Test, Digit Symbol Substitution Test, forward and backward digit span testing). Depression, stress, and anxiety screening will also be performed. Blood samples from all participants will be collected, and aliquots will be immediately stored in a biobank. Primary laboratory outcomes will include serum levels of presumed cognitive dysfunction blood biomarkers SAA, Hcy, S100B, and BDNF. Follow-up will be performed at 12, 24, 36, and 48 months.

**Results:**

Data collection started in December 2021 and is ongoing. So far, 53 patients with IBD have been recruited and 50 HC matched. Data collection should end in January 2030. Intermediary analysis will be performed in April 2024. We expect patients with IBD to have lower scores on cognitive testing and a positive correlation between disease length and cognitive impairment level. In addition, the levels of stress, anxiety, and depression should be higher in the IBD group. The serum levels of the 4 biomarkers could correlate or anticorrelate with cognitive scores and serve as predictive factors for MCI or dementia development. A higher level of education, a younger age, the absence of malabsorption, and good disease control might serve as protectors against MCI.

**Conclusions:**

GBA interactions, along with systemic inflammation and the adverse effects of medication, might be a cause of MCI and AD development in patients with IBD. Serum biomarkers could prove cheap and useful predictors of MCI development.

**Trial Registration:**

ClinicalTrials.gov NCT05760729; https://clinicaltrials.gov/study/NCT05760729

**International Registered Report Identifier (IRRID):**

DERR1-10.2196/50546

## Introduction

### Background

Inflammatory bowel disease (IBD) is a group of chronic conditions characterized by intestinal inflammation. The 2 most common types of IBD are Crohn’s disease (CD) and ulcerative colitis (UC) [1,2]. The exact mechanisms underlying the development of IBD are yet to be fully understood, but they are thought to be the result of a combination of genetic, environmental, and immunological factors. IBD is believed to be caused by an abnormal immune response that first appears in the gut, where the body’s immune system mistakenly attacks the antigens of the healthy gut bacteria, leading to intestinal inflammation and damage to the intestinal barrier. Exposure to certain environmental triggers, such as a diet high in animal fats, smoking, and, most of all, bacterial or viral infections, may increase the risk of IBD. It is believed that the interplay between these factors leads to a self-perpetuating cycle of inflammation and tissue damage, which contributes to the chronic nature of IBD (a so-called vicious cycle). Systemic inflammation plays a role in IBD pathogenesis, which is proven by the beneficial effect of certain anti-inflammatory medications [3].

Clinical manifestations include common digestive symptoms, such as abdominal pain and cramping, diarrhea (which might be bloody), rectal bleeding, weight loss, fatigue, loss of appetite, anemia, nausea and vomiting, dehydration, and fever. In addition to these digestive symptoms, patients with IBD may also experience extraintestinal manifestations, such as joint pain, skin rashes, eye inflammation, and liver disease. The severity and frequency of symptoms can vary greatly between individuals and can also change over time in the same individual. CD carries a higher risk of extraintestinal manifestations, often believed to be caused by one of its pathogenic mechanisms or malabsorption [1,2].

Mild cognitive impairment (MCI) refers to a decline in cognitive abilities that is greater than that in normal aging but certainly not severe enough to interfere with daily life. MCI is often considered a transitional stage between normal aging and more severe forms of cognitive decline, such as dementia. MCI is most commonly characterized by memory problems, such as difficulty in recalling names and recent events, but it can also involve problems with other cognitive abilities, such as language, decision-making, and attention. The impairment of daily activities is a key criterion to diagnosing dementia and the difference between MCI and dementia [4]. Some of the known risk factors for MCI include age, family history, certain medical conditions, lifestyle factors (eg, smoking and excessive alcohol consumption), and certain medications [4]. There are some modern theories that imply inflammation as a mechanism underlying cognitive impairment [5-8]. A diagnosis is typically made based on a thorough medical and neurological evaluation, as well as a comprehensive assessment of the individual’s cognitive abilities. This may involve a battery of tests, such as memory and language tests, as well as brain imaging studies. The most important thing to do when a cognitive impairment is suspected is follow-up over time, as early intervention might stop the progression of the disease [4]. MCI can sometimes progress to Alzheimer’s disease (AD) or other types of dementia, depending on the cause, age, and other factors [9]. AD is a progressive brain disorder that affects memory, thinking, and behavior. It is the most common cause of dementia. The symptoms of AD usually start with mild memory loss but eventually progress to affect thinking, communication, and the ability to perform daily activities. As the disease progresses, patients may become increasingly dependent on others for their care [10]. Some studies have revealed a link between IBD and the development of AD [6,7,11,12]. Vascular dementia is a type of dementia that occurs due to problems in the blood supply to the brain. It is caused by damage to the blood vessels that deliver oxygen and nutrients to the brain, leading to brain injury and reduced brain function. It is often caused by conditions such as stroke, high blood pressure, and heart disease. Risk factors for vascular dementia include age, smoking, diabetes, and a family history of stroke or heart disease [13].

“Stress disorder” is a term used to describe a mental health condition that can develop in response to a traumatic or stressful event. Individuals may experience a range of symptoms, including intrusive thoughts or memories of the traumatic event; nightmares; and avoidance of people, places, or activities that are associated with the trauma. They may also experience physical symptoms, such as a racing heart, sweating, and muscle tension [14]. “Anxiety disorder” is a general term that refers to a group of mental health conditions characterized by excessive and persistent feelings of worry, fear, and unease [15]. Depression is a mental health condition characterized by persistent feelings of sadness, hopelessness, and a loss of interest in activities that were once enjoyable. It is a common and serious condition that can have a significant impact on an individual’s daily life and overall well-being. In addition to feelings of sadness, depression can also cause a range of physical and emotional symptoms, including fatigue, changes in appetite and sleep patterns, difficulty in concentrating, and thoughts of self-harm or suicide. The exact cause of depression is not fully understood, but it is believed to be related to a combination of genetic, biological, environmental, and psychological factors [16-18].

Homocysteine (Hcy) is an amino acid. Studies have shown that individuals with IBD have higher serum concentrations of Hcy compared to healthy controls (HC). The exact reason for this association is not fully understood, but it may be related to nutrient deficiencies caused by the inflammation and malabsorption in the gut that often occur in IBD. There is evidence to suggest that elevated levels of Hcy in the blood are associated with an increased risk of MCI and dementia. High Hcy levels have been linked to damage of the blood vessels in the brain, leading to decreased blood flow and oxidative stress, both of which can contribute to cognitive decline [19-23].

Serum amyloid A (SAA) is an acute-phase protein that is produced by the liver in response to inflammation. Amyloid proteins are abnormal fibrous proteins that can build up in tissues and organs, leading to the formation of amyloid plaques. In some cases, amyloid proteins can also enter the bloodstream and circulate in the body. Elevated levels of SAA can be an indicator of various diseases, such as AD, systemic amyloidosis, and hereditary transthyretin amyloidosis. Studies have shown that SAA can induce neuroinflammation and damage neurons in the brain, which may contribute to the development and progression of AD. In addition, SAA has been found to accumulate in the brain in the form of amyloid plaques, which are a hallmark feature of AD. There is limited research on the relationship between SAA levels and IBD. Some studies have suggested that individuals with IBD may have elevated levels of amyloid proteins in their bloodstream, possibly as a result of chronic inflammation in the gut [24-29].

Brain-derived neurotrophic factor (BDNF) is a type of protein that is important for the growth, maintenance, and survival of neurons in the central nervous system. BDNF plays a key role in processes such as neuroplasticity, learning, and memory formation. Low levels of BDNF have been associated with several neurological and psychiatric disorders, including depression and AD. BDNF plays a role in the inflammation associated with IBD. BDNF levels are modified in IBD, but there is little evidence of the direction [30-33].

S100 calcium-binding protein B (S100B) is a protein that is found in a variety of tissues, including the brain, where it has been implicated in several neurobiological processes, including synaptic plasticity, neurogenesis, and neuroinflammation. High serum S100B levels have been associated with a variety of neurological disorders, including traumatic brain injury, stroke, and neurodegenerative diseases. Studies have shown that S100B levels are elevated in the blood and intestinal tissue of patients with IBD, suggesting that the protein may play a role in the development and progression of the disease. In addition, high levels of S100B have been associated with increased inflammation and oxidative stress [34].

In conclusion, IBD is a combination of intestinal barrier dysfunction and intestinal and systemic inflammation. Due to intestinal barrier dysfunction, the intestinal microbiome is affected in the course of the disease or it is the cause of the disease (IBD). Several studies have shown the relationship between the gut–brain axis (GBA) and the development of depression, affective mood disorders, and stress, which might promote the development of cognitive impairment. Systemic inflammation is known to increase cardiovascular risk, which is a risk factor for cognitive impairment. Other risk factors, such as smoking, alcohol consumption, and other diseases, also promote the development of cognitive impairment. Some studies have suggested a link between IBD and cognitive disorders, while other studies have indicated a link between mood disorders and IBD, and still others have suggested a link between mood disorders and cognitive disorders. Therefore, this might be a vicious cycle.

In this study, blood biomarkers, such as SAA (an inflammatory biomarker, a precursor of beta-amyloid plaques in the brain), Hcy (a pro-inflammatory molecule increased in cognitive disorders), S100B (a neuronal structural protein increased in brain injury), and BDNF (decreased in cognitive disorders) were selected in order to validate the hypothesis that these biomarkers could be used as predictive factors for cognitive impairment associated with IBD. As a summary of the basic knowledge that led to the idea of this study, Figure 1 shows the possible implied mechanisms underlying the development of MCI in patients with chronic IBD.

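### The only analysis named for the markers against cognition is an unadjusted Pearson correlation, so a positive result for S100B or SAA could reflect shared inflammation and would not show a neuronal signal or value beyond routine inflammation markers

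*Protocol article*

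**What the plan says.** The Background section describes the two markers in two ways. Where it justifies their selection, the labels are "S100B (a neuronal structural protein increased in brain injury" and "SAA (an inflammatory biomarker, a precursor of beta-amyloid plaques in the brain". Shortly before, where it introduces each protein, it gives a wider account:

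- **S100B:** "S100 calcium-binding protein B (S100B) is a protein that is found in a variety of tissues, including the brain". It adds: "Studies have shown that S100B levels are elevated in the blood and intestinal tissue of patients with IBD". It also links high levels to more inflammation and oxidative stress.
- **SAA:** "Serum amyloid A (SAA) is an acute-phase protein that is produced by the liver in response to inflammation". On the disease itself it is cautious: "There is limited research on the relationship between SAA levels and IBD".

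The Background also connects inflammation to cognition. It mentions theories in which inflammation underlies cognitive impairment, and says systemic inflammation raises cardiovascular risk, itself a risk factor for impairment.

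Table 1 makes the association of the four markers with cognitive scores a primary objective. Under Power Calculation, Statistical Model, and Data Analysis, that association is assigned a Pearson coefficient. The linear and logistic regressions are directed at risk factors found through the questionnaires. CRP, ESR and fecal calprotectin appear in Table 14 as baseline hospital-registry values, but no stated model uses them. The abstract anticipates: "Serum biomarkers could prove cheap and useful predictors of MCI development".

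**The concern.** By the protocol's own account, inflammation is linked to both markers and to cognition. In IBD patients, a serum level may therefore combine the inflammatory state with any contribution from the brain. A Pearson coefficient cannot separate the two.

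Two readings of a positive result are at stake. One is that S100B indicates neuronal injury, which its selection label invites. The other is that a dedicated assay tells a clinician something that routine CRP does not, which matters if the markers are to be recommended as cheap and useful. An unadjusted correlation supports neither, although the data needed to examine both are already listed for collection.

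**Working it through.** **The plan's own figure.** The only power calculation concerns the MOCA group difference: 2 points, SD 3.0, two-sided alpha .05, power 80%, with 52 cases and 26 controls.

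- Controls at 2:1 = (1 + 1/2) × [3 × (1.960 + 0.842) / 2]² = 26.5; cases = 2 × 26.5 = 53.0.
- At 26 and 52 the power is 79.3% by the normal approximation.

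The stated figure is therefore reproduced to within rounding. It does not cover the marker analysis and has no bearing on this point.

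**Inputs for the marker analysis.** From the document: 100 IBD patients and a two-sided .05 level. Assumed, because the document gives no correlations: inflammation with marker, a = 0.3, 0.5, 0.7; inflammation with cognition, b = 0.2, 0.3, 0.4 (absolute values); no direct marker-cognition link.

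**Formulas.**

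- Induced correlation: r = a × b.
- Chance of a significant Pearson test, by Fisher z: m = atanh(r) × √(100 − 3); probability = Φ(m − 1.96) + Φ(−m − 1.96).

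**Results.**

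| a | b | r | significant |
|---|---|---|---|
| 0.3 | 0.2 | 0.06 | 9% |
| 0.3 | 0.3 | 0.09 | 14% |
| 0.3 | 0.4 | 0.12 | 22% |
| 0.5 | 0.2 | 0.10 | 17% |
| 0.5 | 0.3 | 0.15 | 32% |
| 0.5 | 0.4 | 0.20 | 52% |
| 0.7 | 0.2 | 0.14 | 28% |
| 0.7 | 0.3 | 0.21 | 56% |
| 0.7 | 0.4 | 0.28 | 81% |

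Worked ends of the range:

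- r = 0.06: m = 0.0601 × 9.849 = 0.592; Φ(−1.368) + Φ(−2.552) = 0.086 + 0.005 = 0.091.
- r = 0.28: m = 0.2877 × 9.849 = 2.833; Φ(0.873) = 0.809, and the other tail is negligible.

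**After adjustment.** The numerator of the partial correlation of marker and cognition given inflammation is r − a × b = 0. In this model a test adjusted for well-measured inflammation rejects at 5%. CRP measures inflammation imperfectly, so in practice some of the induced association would remain.

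**If both groups are pooled.** The document does not say whether the correlation is computed within groups. Suppose there is no association within either group, cognition is shifted by the protocol's own 2/3 SD, and the marker is shifted by an assumed d. Then r = (1/3 × d/2) / √[(1 + 1/9)(1 + d²/4)]. For d = 0.25, 0.5, 1.0 and 1.5, r = 0.04, 0.08, 0.14 and 0.19, significant in 8.5%, 19%, 52% and 77% of studies with 200 participants. The group difference alone can produce the correlation.

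**The case against.** The strongest reply is that prediction is not causation. If SAA follows inflammation and inflammation follows cognition, SAA does predict cognition. A reader might infer that the planned analysis cannot support any predictor claim. The documents do not bear that out: the stated aim is prediction, which requires neither a brain source nor independence from inflammation.

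A reader might also take 9-81% as an inflated false-positive rate. It is not one. Under the assumptions the correlation really is non-zero, so the figures are chances of detecting a real correlation that arises only through inflammation. What could be false is the interpretation, not the test result.

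Nor should the protocol be read as hiding the inflammatory nature of SAA, which its selection text calls inflammatory outright. It does not say that SAA comes from liver inflammation or that the gut is the source of serum S100B, and its statement on SAA in IBD is hedged. S100B is the clearer case. No section commits the authors to concluding neuronal injury from S100B; its label merely invites that reading.

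Three further replies carry some weight:

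- **Flares.** Table 3 defers testing until an acute flare is over. This should narrow differences in inflammation but does not remove them, and disease activity is still scored at every visit.
- **Mediation.** Systemic inflammation is part of the hypothesised route to impairment, so adjustment may remove part of the effect of interest. This is a reason to show both estimates.
- **Condensed article.** A full covariate list may exist elsewhere, and the text does not forbid laboratory covariates. The point therefore rests on the method the article does name for a primary objective, not on a missing list.

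**Conclusion.** The point holds as a limit on interpretation. The short neuronal label for S100B is narrower than the document's own description, and the unadjusted correlation named for both markers cannot separate a brain-related signal from shared inflammation or show value beyond CRP, ESR or calprotectin.

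Over the assumed ranges, inflammation alone would produce a within-IBD correlation of 0.06-0.28, significant in about 9-81% of studies of 100 patients. The width reflects assumed inputs; only the sample size and test level come from the document. A significant result could still be reported as a plain predictive association. This is a cheap improvement to the analysis, not a defect that undermines the study.

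**What to change.** Within the IBD group, report each association of S100B and SAA with the cognitive scores in two forms: unadjusted, and from a regression that adds baseline CRP and, where available, fecal calprotectin. Alongside, give the gain over a model with CRP alone, as R-squared for the scores and AUC for MCI. State in advance that neuronal-specific or added-value conclusions will go no further than the adjusted result supports, and that the unadjusted result may support a plain predictive association. Amend the selection text so that the S100B label matches its fuller description in the Background.

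The cost is a paragraph in the analysis plan and covariates already listed in Table 14, with no new visit, assay or participants. There are two downsides. If inflammation is a mediator, the adjusted estimate excludes that path, so neither estimate should be shown alone. The inflammation values come from the hospital registry and may be incomplete or not taken on the day of the study sample, so the number available and the time between samples should be reported.

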**Figure 1 figure1:**
[figure not shown]
Possible mechanisms underlying the development of cognitive impairment associated with IBD. IBD: inflammatory bowel disease.

## Methods

### Study Design

The study will be a single-center, prospective, observational, analytic study with a group of at least 100 patients with a diagnosis of certainty of IBD and a group of at least 100 HC. The study is part of a PhD thesis, and funding was obtained from the parent university.

### Sites, Population, and Case and Control Definitions

The study will take place in Cluj-Napoca, Romania, in the Clinical CF Hospital and the Regional Institute for Gastroenterology and Hepatology “Octavian Fodor.” An agreement was obtained from all the participant clinics.

Two separate groups consisting of at least 100 patients with IBD and at least 100 HC will be recruited. The study will be carried out from May 2021 to January 2030. The HC will be matched with the patients with IBD based on age, sex, and education.

Patients included in the case (IBD) group need to have a clear diagnosis of IBD. For this, a histopathological examination proof will be obtained from the databases of the participant centers or from the personal records of the patients (if the site does not have the original proof diagnosis).

The HC will be recruited from the day care hospital and ambulatory. Their diagnosis must have never been IBD, and they should be in good health at the moment of inclusion.

The inclusion criteria are listed in Table 2 and the exclusion criteria in Table 3.

**Table 2 table2:** Inclusion criteria.

Study group	Inclusion criteria
IBD^a^	Males and females aged over 18 years Patients with a confirmed IBD diagnosis Written informed consent obtained
HC^b^	Males and females aged over 18 years Good level of health Written informed consent obtained

^a^IBD: inflammatory bowel disease.

^b^HC: healthy controls.

**Table 3 table3:** Exclusion criteria.

Exclusion criteria		Details
**Absolute exclusion criteria**		
	Prior stroke or myocardial infarction or cardiac arrest	Patients with known stroke and myocardial infarction are already known to have an accelerated cognitive decline rate due to a vascular mechanism. Postanoxic encephalitis after cardiac arrest carries an additional risk of cognitive decline.
	Severe organ failure	This includes the presence of end-stage respiratory, liver, renal, and cardiac diseases.
	Familial AD^a^	Patients with known familial AD develop the disease at an earlier age.
	Concomitant past and current neurological disorders	These include epilepsy, encephalopathy due to any cause, history of severe head trauma, history of encephalitis, multiple sclerosis, Parkinson’s disease, brain tumor, and dementia due to any cause.
	Pregnancy	Pregnant women will not be included because they carry potentially other risks and might be stressed about their situation.
	Prior psychiatric disorders and chronic use of neuroleptics and anticholinergic medication	These include all psychiatric pathologies, including depression, anxiety disorder, attention deficit hyperactivity disorder, autism spectrum disorders, posttraumatic stress disorder, schizophrenia, personality disorders, and alcohol and drug abuse. Also in this category is the use of neuroleptics, which are drugs that decrease cerebral function, although they might interfere with cognitive testing, depending on dose. Anticholinergic medication might slow cognitive functioning.
	Unclear diagnosis	Patients with an unclear diagnosis will not be recruited as they might have a different pathology.
	Involvement in clinical trials	Participation in clinical trials for medication might interfere with the study results because of the unknown side effects of the medication or other factors.
	Current and past history of neoplasia	Patients with neoplasms already have a poor performance status, and this might negatively influence the results of this study. in addition, the medication might interfere with cognitive testing.
	Use of vitamin B12 and B9 supplements	Vitamin B12 and B9 supplements might decrease serum levels of Hcy^b^.
	Short bowel syndrome	Intestinal resection carries the risk of malabsorption and might be a cause of cognitive impairment.
	Diabetes mellitus	Diabetes mellitus carries an additional risk of MCI^c^.
	Hypothyroidism	Hypothyroidism leads to decreased brain performance.
	Prior diagnosis of atrial fibrillation	Patients with known atrial fibrillation are at greater risk of cognitive dysfunction due to microembolic events.
	Uncontrolled arterial hypertension	Patients with uncontrolled hypertension carry an additional risk of cognitive dysfunction.
